### Intervention

All patients will receive current routine pharmacological treatments and an 80 min rehabilitation therapy session that combines physical therapy for upper limb function, neuromuscular electrical stimulation, occupational therapy and rTMS therapy. Over the course of 2 weeks, all treatments will be administered once daily, 5 days a week (10 sessions in total). The relevant period segments of the experiment are shown in Figure 2.

**Figure 2 F2:**
[figure not shown]
Schedule of participant enrolment, interventions and assessments. LF-rTMS, low-frequency repetitive transcranial magnetic stimulation; cM1, contralesional primary motor cortex; HF-rTMS, high-frequency repetitive transcranial magnetic stimulation; cPMd, contralesional dorsal premotor cortex; FMA-UE, Fugl-Meyer assessment of upper extremity; AMI, Arm Subscore of the Motricity Index; FTHUE-HK, Hong Kong edition of Functional Test for the Hemiplegic Upper Extremity; MBI, Modified Barthel Index; MAS, Modified Ashworth Scale; fMRI, functional MRI.

rTMS will be applied with a Magneuro 100 magnetic stimulator (Vishee Medical Technology Co., Ltd., Nanjing, China) using a figure-of-eight-shaped coil for accurate targeted treatment. The centre of the coil will be tangential to the treatment plane, and the handle will be positioned at 45° from the sagittal plane. Using the surface electromyography data that will be collected from the abductor pollicis brevis on the uninjured side, the potential difference between the highest and lowest peaks will be selected to obtain the motor-evoked potential (MEP). The minimal intensity required to generate at least 5 out of 10 MEPs in a relaxed target muscle that are >50 µV is known as the resting motor threshold (RMT).^24^ The group A strategy will use rTMS (1 Hz) over cM1, 90% RMT, 120 trains of 10 s duration, 2 s intertrial intervals, 1200 pulses per session and a 23 min, 58 s total duration. The group B strategy will use rTMS (10 Hz) over cPMd, 90% RMT, 80 trains of 1.5 s duration, 10 s intertrial intervals, 1200 pulses per session and a 15 min, 10 s total duration. The coil positioning will be guided throughout the experiment using a neuronavigation system (Visor2 ANT, Germany).^25^ For a period of 2 weeks, each patient will receive rTMS once each day (5 days each week).

#### Outcome assessment

#### Outcome Assessment

#### Primary outcome

FMA-UE will be used to evaluate performance-based motor functions of the paralysed upper limbs. The FMA-UE consists of 9 major items and 33 subitems. Each item receives a rating between 0 and 3, and the total score ranges from 0 (no movement) to 66 (normal active movement). A higher score indicates lower motor impairment.^26^

#### Secondary outcomes

##### Clinical and functional assessments

AMI includes shoulder abduction, elbow flexion and pinch grip strength. The overall score of the scale is calculated by summing the scores of the three components (the highest score for each item is 33 points) and 1 point, so that a total of 100 points is reached. The score is positively correlated with the motor performance of the upper limb.^27^

FTHUE-HK includes 12 test items with seven functional levels that evaluate upper limb function as a whole. The condition in which the patient has completed the test for this level is determined according to the requirements of each level.^28^ A higher level indicates that the patients have better upper extremity motor function and a greater capacity for using the upper limbs during daily activities.

MBI^29^ is a 10-item rating scale that measures the quality of general life activities. The higher the score, the more independent the patients are in their daily lives. Scores >60 indicate a high likelihood of performing ADLs and maintaining a standard of living.

Modified Ashworth Scale (MAS) is the most widely used clinical scale to assess the increase in muscle tone after central nervous system lesions, which is manifested by increased resistance of joints to passive movement. According to the MAS, possible scores range from 0, 1, 1^+^, 2, 3 to 4, with 0 reflecting normal tone and 4 reflecting fixed muscle contracture.^30^

##### DTI and fMRI indicators

Magnetic resonance (MR) scanning will be performed using a 3.0T MR scanner (Discovery 750W, GE Healthcare, USA) and a 24-channel head coil. In addition to T2-weighted image (WI) scans to exclude parenchymal brain lesions and abnormalities, anatomical images will be obtained using a 3D gradient-echo pulse sequence to collect T1WI in the sagittal plane. The following will be the parameters: repetition time (TR)=8.5 ms, time echo (TE)=2.52 ms, inversion time=450 ms, field of view (FOV)=256×256 mm², matrix size=256×256, flip angle=12°, image matrix=128×128, number of excitations (NEX)=1, bandwidth=31.25 kHz, 1.0 mm thick slices and 192 slices. Data Processing Assistant Resting-State fMRI software (http://rfmri.org/DPARSF) will be used to preprocess the functional imaging data. DTI determines lesion size and fractional anisotropy (FA) within the posterior limb of the internal capsule (PLIC) to assess the integrity of the CST.^31^ DTI is based on an echo-planar imaging sequence. The parameters will be as follows: TR=8000 ms, TE=96 ms, image matrix=112×112, FOV=22.4×22.4 cm², b=0 and 1000 s/mm², NEX=2, slice thickness=3 mm, interslice spacing=0 mm and *acceleration* factor*=*2. FA values and the mean FA Asymmetry Index (FAAI) are the leading indicators of tract integrity. FAAI=(FAunaffected−FAaffected)/(FAunaffected+FAaffected).^32^ FAAI is in the range of −1.0 to +1.0.

### Statistical analysis

#### Clinical data analysis

Statistical analysis will be employed using SPSS statistical software (V.22.0, Chicago, IL, USA). Prior to entering data for descriptive statistics, the Shapiro-Wilk test will be used to verify normal probability. Data from the normal distribution will be given as mean and SD, but data from the non-normal distribution will be expressed as medians with IQR. Categorical variables will be described as a function of frequency as a percentage. Demographic characteristics and baseline variables will be assessed for between-group differences using statistical tests appropriate for the data type. Specifically, independent sample t-tests or non-parametric Mann-Whitney tests will be used for continuous variables, while chi-square or Fisher’s exact tests will be employed for categorical variables. Repeated-measure analysis of variance will be used to estimate the therapeutic effect for primary (eg, FMA-UE) and secondary outcomes (eg, list all secondary outcomes here). Statistical significance is defined as p <0.05. The primary analysis will employ an intention-to-treat method to address non-adherence. The absence of primary outcome data will be addressed by utilising baseline data as a reference point and conducting additional sensitivity analyses. The utilisation of a randomised design precludes the use of multivariable models for confounding adjustment. Consequently, the absence of covariates will have no impact on the primary analysis.

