#### Imaging data analysis

DTI datasets will be processed using the Pipeline for Analyzing Brain Diffusion Images (PANDA) toolkit (http://www.nitrc.org/projects/panda) to obtain the average FA and FAAI values of patients from the whole group.^33^ The PANDA process involves three major steps: preprocessing, producing diffusion metrics and constructing networks. The bilateral PLIC, pons and precentral gyrus are selected as regions of interest. Comparisons within groups will be performed using paired t-tests and those between groups using two-sample t-tests. Structural and functional connectivity will be processed using the Infinitome software (Omniscient Neurotechnology (2020) Infinitome). The statistical significance level is set at p <0.05.

For the Human Connectome Project Multimodal Parcellation maps, specific topic versions will be produced using a machine-learning approach. Depending on the paired functioning connection among each participant’s brain maps, it will be used to model their diagnostic classification and neuropsychological examination results. A ‘boosted trees’ method will be applied to every case by the eXtreme Gradient Boosting (XGB) Classifier to adapt the model. This strategy offers better predictive capabilities than using a single tree.

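### The clinical secondary outcomes are assigned to repeated-measures ANOVA through an unfilled placeholder, which leaves the Modified Ashworth result dependent on an unstated score for grade 1+

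*Protocol article*

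**What the plan says.** Under Clinical data analysis the article gives one method for treatment effects on clinical outcomes: "Repeated-measure analysis of variance will be used to estimate the therapeutic effect for primary" and "secondary outcomes (eg, list all secondary outcomes here". The bracket after the word secondary still holds the drafting instruction in place of a list.

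The abstract and the Secondary outcomes section identify the clinical measures this must cover: AMI, FTHUE-HK, MBI, and MAS of the pectoralis major and biceps brachii. For MAS, "possible scores range from 0, 1, 1^+^, 2, 3 to 4", "with 0 reflecting normal tone and 4 reflecting fixed muscle contracture". For the hand function test, "FTHUE-HK includes 12 test items with seven functional levels".

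Two other sentences in the same section could be taken as a fallback:
- "Prior to entering data for descriptive statistics, the Shapiro-Wilk test will be used". This ties the normality test to how data are described.
- "Demographic characteristics and baseline variables will be assessed for between-group differences using statistical tests appropriate for the data type". The t-test or Mann-Whitney choice that follows elaborates this sentence on baseline comparisons.

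The DTI measures are handled separately, under Imaging data analysis: "Comparisons within groups will be performed using paired t-tests and those between groups using two-sample t-tests".

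**The concern.** ANOVA works on numbers, and 1+ is an ordered category without one. The MAS analysis cannot be run as written until someone assigns it a score, and the common choices are not rescalings of each other, so both the estimate and the p-value can move. For FTHUE-HK the levels can be numbered 1 to 7 without inventing anything. There the concern is only that ANOVA treats each step as equally large.

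The placeholder suggests that methods were not matched to outcomes one by one. At baseline the plan asks for tests suited to the data type. For treatment effects it states no such principle. At stake are the spasticity and functional-level results, which are secondary.

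**Working it through.** **1. The plan's own figure.** The only design figure is 42 completers for FMA-UE (d = 0.45, two-sided 0.05, 80% power). It reproduces as a 2×2 repeated-measures interaction with f = d/2 = 0.225 and an assumed pre-post correlation of 0.5, which the article does not state: λ = f²·N·m/(1−ρ) = 0.225² × 42 × 2 / 0.5 = 8.5, power 81.2%. It concerns the primary outcome only, and nothing below depends on it.

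**2. What is fixed and what is open.**

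| Item | Article |
|---|---|
| Treatment-effect method, clinical secondary outcomes | Repeated-measures ANOVA only |
| List of outcomes in that sentence | Placeholder |
| Numeric value for MAS 1+ | None given |
| Rank or ordinal method for treatment effects | None given |
| Shapiro-Wilk | Descriptive statistics |
| Mann-Whitney, chi-square, Fisher | Baseline comparisons |

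**3. Why the coding matters for MAS.** Compare 1+ = 1.5, giving {0, 1, 1.5, 2, 3, 4}, with renumbered grades {0, 1, 2, 3, 4, 5}.

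| Change in one patient | 1+ = 1.5 | 0 to 5 |
|---|---|---|
| 2 to 1+ | 0.5 | 1 |
| 2 to 1 | 1 | 2 |
| 3 to 2 | 1 | 1 |

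Some steps double and others do not, so this is more than a change of unit. Relative to a 3-to-2 improvement, a 2-to-1 improvement counts equally under one coding and double under the other.

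**4. Size, under stated assumptions.** The article gives no MAS distribution. Assumed: grade proportions 0.30, 0.25, 0.20, 0.15, 0.08, 0.02; latent normal scores with pre-post correlation 0.64; a latent shift of −0.5 in one arm; 22 per arm; 20,000 simulated trials. With two assessments, the group-by-time test equals a t-test on change scores.

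| Coding | Mean group difference in change | p<0.05 |
|---|---|---|
| 1+ = 1.5 | −0.426 | 34.9% |
| 0 to 5 | −0.584 | 34.4% |
| 1+ = 1 | −0.399 | 31.1% |

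- Ratio of the first two mean effects: 0.584/0.426 = 1.37. Largest ratio across the three: 0.584/0.399 = 1.46.
- The p<0.05 verdict differs between the first two codings in about 7% of trials, and somewhere among the three in about 14%.
- With no effect, the first two codings disagree in about 2% of trials.

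**5. Does ANOVA keep its size?** With no effect, type I error was 4.8% under each MAS coding. For a seven-level scale with 55% or 75% of patients at the lowest level it was 4.8% and 4.7%.

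**6. Baseline adjustment.** In the same MAS scenario, adjusting the post-treatment score for baseline raised power from about 35% to about 45%. That gain comes from the adjustment. An unadjusted rank test does not share it.

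**The case against.** The article condenses a fuller protocol, and an analysis plan may exist. A numeric value for 1+ is a detail that could be set there. This stands in part: a reader might infer that the coding will be chosen after seeing the data, and the article cannot show that. But the article does not simply leave the method open. It names a method that does not fit one of its outcomes, in a sentence that still holds a drafting instruction.

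Three stronger readings are tempting and fail:

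- **ANOVA is prescribed for every secondary outcome.** The DTI measures sit under Secondary outcomes and get t-tests. The point covers the clinical outcomes only. MAS and FTHUE-HK are not named in the sentence; they fall under it as secondary outcomes.
- **The MAS effect could differ by a factor of two.** That is true of one patient moving between grades 1 and 2. The simulated trial-level effect differs about 1.4-fold, and much of that is scale: the standardised effects are −0.483 (1+ = 1.5) and −0.479 (0 to 5), with nearly equal power.
- **Normal-theory inference breaks down because patients with FMA-UE of 22 or less cluster at low functional levels.** Clustering is plausible, but the article gives no FTHUE-HK distribution, and type I error stayed near 5% even with heavy clustering.

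It can also be said that ANOVA on ordinal scales is common and often tolerable. The type I error results agree, but this supplies no value for 1+.

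**Conclusion.** The point holds in a limited form. The treatment-effect sentence is unfinished, and as written it applies ANOVA to MAS without fixing the score that ANOVA needs. For FTHUE-HK only the equal-spacing assumption is in question.

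Under the assumed grade proportions the consequence is moderate: about a 1.4-fold difference in the mean MAS effect between the two main codings, and a changed significance verdict in about 7% of trials (14% across three codings). The exact sizes move with the assumed distribution, correlation and shift; the dependence on coding does not go away. There is no sign of inflated type I error, and the FMA-UE analysis is untouched. This is a cheap improvement to the secondary analyses and does not threaten the trial's main conclusion.

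**What to change.** Replace the placeholder with a list of named outcomes, each with its method.

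- **MAS (pectoralis major and biceps brachii) and FTHUE-HK:** a van Elteren test stratified by the disease-course stratum used at randomisation, with 1+ as the ordered category between 1 and 2. State beforehand whether it is applied to the post-treatment grade or to the change in ordered category. The post-treatment grade needs no scores at all. Change in category counts steps, which is the 0-to-5 numbering before ranking.
- **Sensitivity analysis for these two scales:** proportional-odds regression. It should not be the main analysis, because cells will be sparse with 44 patients.
- **AMI and MBI:** ANCOVA on the post-treatment score with baseline and stratum. The reason is precision, not ordinality. The section's remark ruling out multivariable models for confounding adjustment should then be reworded, so that it does not appear to forbid this.

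The cost is analysis wording only; no added visits, data or patients are needed. MAS and FTHUE-HK effects would be reported as rank-based estimates, not mean differences, and the rank test should not be expected to gain power over ANOVA. Its merit is that the result on post-treatment grade cannot depend on a score for 1+.

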#### Imaging data analysis

DTI datasets will be processed using the Pipeline for Analyzing Brain Diffusion Images (PANDA) toolkit (http://www.nitrc.org/projects/panda) to obtain the average FA and FAAI values of patients from the whole group.^33^ The PANDA process involves three major steps: preprocessing, producing diffusion metrics and constructing networks. The bilateral PLIC, pons and precentral gyrus are selected as regions of interest. Comparisons within groups will be performed using paired t-tests and those between groups using two-sample t-tests. Structural and functional connectivity will be processed using the Infinitome software (Omniscient Neurotechnology (2020) Infinitome). The statistical significance level is set at p <0.05.

For the Human Connectome Project Multimodal Parcellation maps, specific topic versions will be produced using a machine-learning approach. Depending on the paired functioning connection among each participant’s brain maps, it will be used to model their diagnostic classification and neuropsychological examination results. A ‘boosted trees’ method will be applied to every case by the eXtreme Gradient Boosting (XGB) Classifier to adapt the model. This strategy offers better predictive capabilities than using a single tree.

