**Trial registration number:**

ChiCTR2000038049

STRENGTHS AND LIMITATIONS OF THIS STUDYThis will be a single-blind, controlled, randomised clinical study to compare high-frequency repetitive transcranial magnetic stimulation (rTMS) over contralesional dorsal premotor cortex (cPMd) and low-frequency rTMS over contralesional primary motor cortex (cM1) in severe ischaemic stroke.We will use neuronavigation to position the site of cPMd and cM1 stimulation.Additionally, various outcome measures, including clinical function and functional MRI, will be included to investigate the therapeutic effects of rTMS and its underlying neuroplasticity mechanisms.Because of low-frequency rTMS to the cM1 ranked as an A-level recommendation for improving motor function after stroke, no blank control group undergoing sham transcranial magnetic stimulation (TMS) will be set up.Given the nature of TMS interventions, blinding operators is not feasible.

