The effectiveness of repetitive transcranial magnetic stimulation (rTMS) as ischaemic stroke rehabilitation therapy has been thoroughly studied.^6 7^ This technique promotes brain plasticity by providing continuous magnetic pulses to the brain.^8^ After stroke, neuroplasticity-induced cortical reconfiguration is necessary for the restoration of motor performance.^9^ According to widespread consensus, low-frequency (≤1 Hz) rTMS (LF-rTMS) can reduce neuronal activity and cortical excitability, whereas high-frequency (≥5 Hz) rTMS (HF-rTMS) has the opposite effect.^10^ The interhemispheric inhibition (IHI) model is the foundation of the current rTMS intervention method to support the improvement of upper extremity performance in stroke patients.^11^ It indicates that decreased excitability of the lesioned primary motor cortex (M1) region after stroke results from ‘double obstacles’, including the ipsilateral areas and excessive inhibition in the contralateral areas.^12^ Therefore, lowering IHI by minimising the excitation of the contralesional side will improve recovery.^13^ The IHI model currently serves as the foundation for recommendations regarding the application of rTMS in stroke recovery, with low-frequency rTMS to the contralesional M1 (cM1) ranked as an A-level recommendation for improving motor function.^10^ Because the heterogeneity of patients is not taken into account, the clinical efficacy of this rTMS intervention strategy for poststroke motor dysfunction is limited.^10^ However, for patients with severe stroke with low structural retention, using the vicariation model may be preferred, which posits that the activity in the remaining network locations compensates for the loss of certain capabilities in damaged areas.^14^

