To this end, this randomised controlled clinical trial aims to investigate whether the excitatory rTMS protocol over cPMd has a better effect than the inhibitory rTMS protocol over cM1 to compensate for the limitations of its inconsistent therapeutic effects. In addition to common clinical scales for evaluating upper limb motor function, diffusion tensor imaging (DTI) and fMRI will be used to explore changes in structural and functional connectivity, analyse the correlation between clinical function assessments and neuroimaging data and further elucidate the neurological mechanisms underlying poststroke upper limb rehabilitation.^21^ Several previous investigations have shown that cM1 inhibition does not significantly increase the rehabilitation of upper extremity movements in severe stroke patients.^16 22^ As a result, we hypothesise that the excitatory rTMS protocol over cPMd might be an effective therapy for the recovery of upper extremity motor performance following severe ischaemic stroke. This research may offer significant novel clues into the clinical effects of rTMS in the treatment of upper extremity impairment in ischaemic stroke patients and the underlying neuroplasticity mechanisms of TMS intervention.

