### Participants

#### Inclusion criteria

The following are the inclusion criteria: (1) ischaemic stroke confirmed by CT and/or MRI meets the diagnostic criteria for cerebral infarction in the cerebrovascular disease; (2) primary or unilateral onset or previous onset without residual neurological dysfunction; (3) stable vital signs and clear consciousness; (4) the age ranges from 40 to 70 years; (5) the course of disease ranges from 1 week to 3 months; (6) paralysis of the upper limbs; (7) FMA-UE score ≤22; and (8) the selected candidate or their relatives sign the informed consent form.

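### Within-arm paired t-tests on imaging cannot separate rTMS from natural recovery and rehabilitation; mechanism conclusions should rest on a baseline-adjusted comparison between arms

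*Protocol article*

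**What the plan says.** The Imaging data analysis section of the protocol article plans two kinds of test in one sentence: "Comparisons within groups will be performed using paired t-tests and those between groups using two-sample t-tests". The threshold is common to both: "The statistical significance level is set at p <0.05". The section does not say which comparison carries the mechanism conclusion, or whether the two-sample test is applied to post-treatment values or to change.

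The aim is worded in more than one way. The strengths and limitations list says that clinical and imaging measures "will be included to investigate the therapeutic effects of rTMS and its underlying neuroplasticity mechanisms". The Introduction speaks of "the underlying neuroplasticity mechanisms of TMS intervention" and also, more broadly, of using imaging to "further elucidate the neurological mechanisms underlying poststroke upper limb rehabilitation".

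The setting is fixed elsewhere in the article. Under Inclusion criteria, "the course of disease ranges from 1 week to 3 months". Under Intervention, everyone receives drug treatment and a daily session combining physical therapy, electrical stimulation, occupational therapy and rTMS, ten sessions in all. Both arms are active rTMS. The absence of a sham or placebo arm is disclosed with reasons.

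**The concern.** A paired t-test asks whether a measure changed over the two weeks, not why. The Introduction itself ties brain reorganisation to recovery: "After stroke, neuroplasticity-induced cortical reconfiguration is necessary for the restoration of motor performance". Patients this early after stroke may reorganise through natural recovery or rehabilitation, and no arm goes without stimulation to show how much. A significant paired result for FA, FAAI or connectivity therefore cannot be assigned to rTMS, and correcting p values for multiplicity would not change that.

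There is a second trap. With two paired tests side by side, significance in one arm only is easily read as a difference between the protocols. Two arms with the same true change can produce that pattern often.

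At stake is the mechanism conclusion: a change shared by both arms could be reported as the way cPMd or cM1 stimulation works.

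**Working it through.** The plan states no power or error figure for imaging, so there is none to reproduce. The check asks how often the paired tests are significant when rTMS does nothing and both arms share the same natural change.

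**Inputs**
- Patients per arm: 22 randomised (Sample size section); 21 per arm are expected to complete.
- Test: paired t-test at p<0.05, taken as two-sided (Imaging data analysis).
- Shared natural change *d*, in SDs of the change score: not in the documents. Assumed range 0 to 0.8.
- Normally distributed changes with equal SD, and independent arms: assumed.

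**Formulas**
- One given arm significant: *p* = P(|T| > t for 0.975 on 21 df), where T is noncentral t with 21 df and noncentrality *d*√22. At *d* = 0.5 the noncentrality is 0.5 × 4.69 = 2.35, and *p* = 0.609.
- At least one arm: 1 − (1 − *p*)². At *d* = 0.5: 1 − 0.391² = 0.847.
- Exactly one arm: 2*p*(1 − *p*). At *d* = 0.5: 2 × 0.609 × 0.391 = 0.476.

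**Results, 22 per arm, no rTMS effect**

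| Shared change (SD of change) | Given arm | At least one arm | Exactly one arm |
|---|---|---|---|
| 0 | 0.05 | 0.0975 | 0.095 |
| 0.2 | 0.15 | 0.27 | 0.25 |
| 0.3 | 0.27 | 0.47 | 0.39 |
| 0.5 | 0.61 | 0.85 | 0.48 |
| 0.8 | 0.95 | 0.997 | 0.10 |

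With 21 per arm, the row for 0.5 SD becomes 0.59, 0.83 and 0.49.

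**Reading the table.** When *d* is above 0 the paired test is detecting a real change, so these figures are power, not type I error. The problem is the cause assigned to the change. The zero-change row is the right comparator for each column: 0.05, 0.0975 and 0.095.

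**The between-arm test.** In 40,000 simulated trials per setting, a two-sample t-test on change scores was significant in 0.049, 0.048 and 0.048 of trials at a shared change of 0, 0.5 and 0.8 SD. The shared change cancels.

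**What the baseline scan adds.** Let *r* be the correlation between the two scans (not in the documents). Relative to comparing post-treatment values alone, the variance is 2(1 − *r*) for change and 1 − *r*² for the baseline-adjusted value. At *r* = 0.5 these are 1.00 and 0.75; at *r* = 0.7 they are 0.60 and 0.51; at *r* = 0.8 they are 0.40 and 0.36.

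**The case against.** The strongest reply is that the randomised comparison is already planned, in the same sentence as the paired tests. That is correct. A reader might infer that the mechanism aim is tested by paired t-tests alone, or that the between-arm test is secondary; the text supports neither. What stands is that the sentence gives no order of priority.

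A reader might also infer that within-arm change will be credited to rTMS. No section says so. One wording of the aim, mechanisms of rehabilitation after stroke, fits a plain description of change under combined treatment. Misattribution is a possibility that the plan leaves open, not one that it announces.

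Third, natural change large enough to matter is assumed. The Introduction says that reorganisation is needed for motor recovery; it does not say that FA, FAAI or connectivity move measurably in two weeks. At zero change there is no excess.

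Fourth, a two-sample test on post-treatment values alone would still be a fair randomised comparison, free of shared recovery. It may lose precision, but it would not be biased. The Clinical data analysis section also names repeated-measures analysis of variance for secondary outcomes, and its group-by-time term would compare change between arms. The imaging section, however, names its own tests and does not refer to it.

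Finally, the missing unstimulated arm is a disclosed choice with reasons and is not the fault here. It does limit what any imaging analysis in this trial can claim.

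**Conclusion.** The point holds as a limit on inference. With both arms stimulated, daily rehabilitation for all, and entry 1 week to 3 months after stroke, a significant within-arm imaging change cannot be attributed to rTMS, although explaining rTMS is one of the stated aims. The randomised contrast can bear a mechanism conclusion, but only about cPMd versus cM1 stimulation.

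The size depends on the unknown natural change. Across 0 to 0.8 SD, a given arm is significant in 5% to 95% of trials without any rTMS effect. The pattern of one significant arm peaks in the middle of the tabulated range, at 48% for 0.5 SD against 9.5% at zero. These figures assume 22 analysed patients per arm, normal changes and the same change in both arms. Imaging is a secondary outcome, so the primary FMA-UE result is unaffected.

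**What to change.** In Imaging data analysis, state that mechanism conclusions for FA, FAAI and connectivity rest on the between-arm comparison of the post-treatment value adjusted for baseline, or of change. The adjusted form is preferable for precision.

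Limit those conclusions to the difference between cPMd and cM1 stimulation, and word the mechanism aim in the Introduction and the strengths list to match.

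Report within-arm change as a mean with a 95% CI, described as change under rTMS, rehabilitation and natural recovery combined, with no conclusion drawn from a test within an arm or from significance in only one arm.

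The cost is a few sentences. Scans, patients and data stay the same. The downside is fewer significant within-arm imaging results to report and a narrower mechanism claim.

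### The imaging classifier has no valid target in this trial, and one p<0.05 level with no stated error control covers the regional, within-arm and connectivity analyses

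*Protocol article*

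**What the plan says.** All of this is in the protocol article.

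- **Classifier.** Under Imaging data analysis, an XGB (boosted-tree) classifier is to be fitted using paired functional connections. On its target the text says "it will be used to model their diagnostic classification and neuropsychological examination results".
- **Regions and measures.** The same section says "The bilateral PLIC, pons and precentral gyrus are selected as regions of interest". Under DTI and fMRI indicators: "FA values and the mean FA Asymmetry Index (FAAI) are the leading indicators of tract integrity".
- **Tests.** "Comparisons within groups will be performed using paired t-tests and those between groups using two-sample t-tests". The text does not say whether the two-sample tests use post-treatment values or changes, or which test carries the conclusion.
- **Connectivity.** "Structural and functional connectivity will be processed using the Infinitome software". The number of connections is not given.
- **Threshold.** Directly after these items: "The statistical significance level is set at p <0.05". No primary imaging contrast, family of tests or correction is named.
- **Status.** The DTI and fMRI indicators stand under Secondary outcomes. The Introduction describes their purpose as exploration, but also as elucidating mechanism, and adds a plan to "analyse the correlation between clinical function assessments and neuroimaging data".

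**The concern.** There are three problems, in order of strength.

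1. The classifier is aimed at quantities that the trial, as described, does not contain. It cannot be run as written, and a target chosen after the data are seen would be post hoc, with at most 44 patients.
2. Separate paired tests in each arm do not compare the treatments. Patients enter 1 week to 3 months after stroke and both arms receive active stimulation plus rehabilitation, so change within each arm is expected whether or not the treatments differ.
3. One 0.05 level applied to several regional measures, with no lead contrast, gives a family-wise error above 5%.

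What is at stake is the credibility of the mechanistic findings. The clinical comparison on the Fugl-Meyer upper-extremity score (FMA-UE) is analysed separately.

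**Working it through.** **Classifier target, section against section.**

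- Diagnosis: Inclusion criteria require "ischaemic stroke confirmed by CT and/or MRI meets the diagnostic criteria for cerebral infarction". Materials and analysis describes two arms, both drawn from this population, with no other group. Diagnosis is therefore a single class, and a classifier needs at least two. Treatment arm is not a diagnosis and is not named as the target.
- Neuropsychological results: the listed clinical outcomes are FMA-UE, Motricity Index arm subscore, FTHUE-HK, Modified Barthel Index and Modified Ashworth Scale. None is a neuropsychological test. Cognition appears only under Exclusion criteria.

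Neither target is available from the data the article describes.

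**Is there a figure to reproduce?** The imaging text states only the 0.05 level. The article's sample size (42 completers, 21 per arm) concerns FMA-UE. It can be reproduced as a repeated-measures interaction with f = 0.45/2 = 0.225 and an assumed correlation of 0.5 (power 0.81). This point does not rest on it.

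**Between-group regional tests.** Assume all three structures are split by side and the asymmetry index (FAAI) is computed for each. That gives 3 × 2 = 6 FA values plus 3 FAAI values, or 9 measures. With every null true and tests independent, the family-wise error is 1 − 0.95^k and the expected number of false positives is 0.05k:

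- k = 3 (FAAI only): 14%; 0.15 expected
- k = 6 (FA only): 26%; 0.30 expected
- k = 9 (both): 1 − 0.95^9 = 37%; 0.45 expected

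FAAI is computed from the two FA values, and neighbouring regions are related, so the tests are not independent. For two-sided tests with jointly normal statistics, the Šidák inequality makes the independence figure an upper bound. Hence up to about 37%. For scale, a Bonferroni threshold for nine tests is 0.05/9 = 0.0056.

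**Within-arm tests.** Suppose both arms change equally and each paired test has power p. The chance that exactly one arm is significant is 2p(1 − p):

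- p = 0.5: 2 × 0.5 × 0.5 = 50%
- p = 0.8: 2 × 0.8 × 0.2 = 32%

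A pattern of change in one arm and not the other is thus common when the treatments do not differ.

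**Connections, only if each pair were tested at 0.05.** K regions give K(K − 1)/2 pairs. The article does not state K, so these are assumptions: K = 20 gives 190 pairs and 9.5 expected false positives; K = 100 gives 4,950 pairs and 247.5.

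**Share of significant results that are false.** With π the proportion of true nulls, the share is 0.05π / (0.05π + power × (1 − π)). A two-sample t-test with 21 per arm at d = 0.45 has about 30% power.

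- 30% power: 14%, 40%, 60% and 76% for π = 0.5, 0.8, 0.9 and 0.95
- 80% power: 6%, 20%, 36% and 54%

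The share passes one half only when π exceeds power/(power + 0.05). That is 0.30/0.35 = 0.86 at 30% power and 0.80/0.85 = 0.94 at 80% power.

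**The case against.** The strongest defence is that this is a condensed article on imaging meant largely as exploration, that multiplicity rules may sit in a full protocol or analysis plan not shown, and that a between-group test is planned alongside the within-arm ones. Much of that stands, and it rules out several stronger readings that a reader might infer:

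- **That most significant imaging findings would be false.** This depends on the share of true nulls and on power. The article gives neither for imaging, and the plausible range is wide (6% to 76% above).
- **That the tests are definitely uncorrected.** The text is silent on correction and does not exclude it. What can be said is that no error control is stated.
- **That many regions are tested.** Three structures are named in advance, and the article singles out the posterior limb of the internal capsule (PLIC) for corticospinal tract integrity.
- **That the DTI family-wise error is 75%.** Counting two within-arm tests and one between-arm test for each of nine measures gives 27 tests and 1 − 0.95^27 = 75%. This treats all 18 within-arm nulls as true, although change within each arm is expected.
- **That connectivity will yield hundreds or thousands of false positives.** No number of connections is given, and the text does not say that each is tested. The only stated use of the paired connections is as input to the classifier.
- **That the authors will infer a treatment difference from within-arm results.** Nowhere do they say so. The weakness is that the plan leaves this open.

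The defence does not reach the classifier. Condensation can omit detail, but it does not explain naming targets that the article's own design and outcome list do not supply. Nor does exploratory intent fully answer the threshold: imaging is listed as a secondary outcome, is meant to explain mechanism, and carries a declared significance level.

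**Conclusion.** The point holds in this form. The classifier has no valid target in the trial as described; this is a mismatch within the article and rests on no assumption. The imaging tests share one 0.05 level with no stated error control. For an assumed nine between-group FA and FAAI tests, this allows a family-wise error of up to about 37%, or 14% to 26% if only three or six are tested, and less with correlation. Within-arm tests cannot support a treatment difference. The matter should be put right because it concerns listed secondary outcomes and the cost is small. It does not touch the primary FMA-UE conclusion, and the documents do not show that the imaging findings would mostly be false.

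**What to change.** 1. Remove the classifier, or retarget it to a collected outcome such as FMA-UE change, with cross-validation, and label it exploratory. FMA-UE change is not a category, so the target would need either a regression form of the method or categories fixed in advance.
2. Base imaging conclusions on the between-group contrast adjusted for baseline. Name one lead measure, for example PLIC FAAI.
3. Apply false discovery rate control to the other regional measures and to any connection-level tests, and state how many there are.
4. Report within-arm changes as estimates with confidence intervals, without p-values.

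If a full protocol or analysis plan already settles the error control, a short cross-reference is enough for item 3. The cost is analysis wording and fewer nominally significant imaging findings. No extra patients, visits or scans are needed.
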